## *Figure 2. Example of possible layout of hotspots (black blocks) and the surrounding areas (grey blocks) where hotspot targeted interventions will be evaluated). The depicted grid cells are 250x250m.*

## d. Intervention

Up to sixteen clusters will be defined as in the example shown in figure 2. Each cluster consists of a hotspot of malaria transmission and the area surrounding the hotspot 500m in each direction. In the entire study area current malaria control interventions will continue without interruption. In the intervention clusters (i.e. half of the identified hotspots), interventions will be superimposed on ongoing control measures: these intervention hotspots will be targeted with IRS, LLINs, larviciding and FSAT. All the intervention measures will be discussed in more detail in section f. ‘Procedures- Intervention Phase’ however, a brief overview is provided below.

*Indoor Residual Spraying (IRS)*

IRS will be carried out twice per year in all households in the intervention hotspots in the period preceding the long rainy season (March 2012) and six months later (September 2012). Meetings will be held with DOMC to discuss the optimal insecticide for use in the context of ongoing IRS activities in the district.

*Long Lasting Insecticide Treated Bednets (LLIN)*

All compounds in intervention hotspots will be visited in March 2012 and each house will receive a Long Lasting Insecticide Treated Nets for each sleeping space. The DOMC will be consulted about which type of LLINs should be distributed and how best to approach this, but activities will be undertaken by study personnel A follow-up visit is planned one month and 6 months after LLIN distribution to provide additional nets where needed and to monitor accurate use.

*Larviciding*

All mosquito larval habitats in all hotspots and evaluation zones will be mapped using handheld GPS systems in January. All habitats found to persist for more than a week within intervention areas will be treated with a larvicide that has been approved by the Pest Control Product Board and by DOMC, *Bacillus thuringiensis var. israelensis* (Bti) and/or *Bacillus sphaericus* (Bs). Larviciding will begin in March 2012 and continue weekly throughout the rainy season (until July 2012).

*Focal screen and treatment (FSAT)*

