   1. YES
   2. NO, REASON_____________
2. Record Barcode number and date on microcontainer

Barcode Number: ________________________**Appendix F: Side effects monitoring form form insecticides**

Ask the head of house whether anyone in the house has suffered from the following symptoms since we sprayed the house/issued bednets

Area (Cell)_____________

Compound/house code_______________

| **Questions** | | | **Response (Y/N/DK)** |
| --- | --- | --- | --- |
| **ENGLISH** (Since we carried out IRS/gave bednets have you had…….. | **LUO** (Nyaka wa kir yath/chiw nede, be isebdo gi….. | **KISWAHILI** (Tangu tunyunyize dawa/gawa neti, je umehisi…… |  |
| **1.Headache** | Wich bar | Kuumwa na kichwa |  |
| **2. Itching/or rash** | Guonyruok/guonyo | Kuwashwa ama harara |  |
| **3. Difficulty in breathing** | Pek mar yueyo | Ugumu wa kupumua |  |
| **4.Dizziness** | Kawirawira | Kusinziasinzia |  |
| **5. Vomiting/nausea** | Ng’ok/chuny lep | Kutapika ama kuchafukwa na moyo |  |
| **6. Stomachache** | Ich kach | Kuumwa na tumbo |  |
| **7.Others/specify** | Mamoko/wachi | Mengineyo/fafanua |  |

If Y is answered to any of the above ask the head of the house which person/s suffered these symptoms and then call up each participant and complete the adverse reporting form. If serious also complete the serious adverse event form.

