**Appendix H: Adverse event forms**

**H1: Adverse event reporting form**

| ADVERSE EVENT REPORTING FORM | | | | | | | CIRCLE AS APPROPRIATE:FSAT/ IRS/LLIN | | | | | | |
| --- | --- | --- | --- | --- | --- | --- | --- | --- | --- | --- | --- | --- | --- |
| **Person ID:**  ___________ | **Cell:** | | | | **Compound/house code:** | | | | **Date:**  \|___\|___\| / \|___\|___\| / \|___\|___\| | | | | |
|  | ***Complete on day first reported*** | | | | ***Complete on day first reported and update as needed*** | | | | | | | ***Complete on final day*** | |
| **Event** | **Date event onset (d)** | **Date event report (e)** | **Name person reporting** | **Max severity* (f)** | | **Max relationship† (g)** | | **Serious? ‡ *(Y/N)*(h)** | | **Episodic?**  ***(Y/N)*(i)** | **Outcome †† (j)** | | **Date event resolved‡‡ (k)** |
|  |  |  |  |  | |  | |  | |  |  | |  |
|  |  |  |  |  | |  | |  | |  |  | |  |
|  |  |  |  |  | |  | |  | |  |  | |  |
|  |  |  |  |  | |  | |  | |  |  | |  |
|  |  |  |  |  | |  | |  | |  |  | |  |

*** Severity:** Rank on scale of 1-4: mild = 1; moderate = 2; severe = 3, life-threatening = 4 **† Relationship:** Rank on scale of 0-4: none = 0; unlikely = 1; possible = 2; probable = 3; definite = 4

**‡ Serious:** Criteria for SAE: fatal, life-threatening, results in or prolongs hospitalization, results in significant or persistent disability or capacity requires medical / surgical intervention to prevent serious outcome.

If serious, report to core facility staff immediately.

**†† Outcome:** Rank on scale of 1-5: resolved without sequelae = 1; resolved with sequelae = 2; AE still present at study end/discontinuation, but improving = 3; subject died = 4; unknown = 5

**‡‡ Date event resolved:** Complete on Day 42 – If AE still ongoing at end of follow-up, indicate in question.

| SERIOUS adverse event form – initial report | | **Date of SAE Report:**  \|____\|____\|/\|____\|____\|/\|____\|____\|  *day month year* | | | |
| --- | --- | --- | --- | --- | --- |
| **Person ID:**  \|_____\|_____\|_____\|_____\|_____\|_____\|_____\| | | **Date enrolled:**  \|____\|____\|/\|____\|____\|/\|____\|____\|  *day month year* | | | |
| **Person name:** | | **Age:** \|_____\|_____\| years | | **Gender:**  Male Female | |
| **Parent name:** | |  | | | |
| **Event description**:__________________________________________________________________________________________________  *(symptom, sign, or laboratory abnormality)* | | | | | |

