| **Indicate reason for serious AE**  *(tick all that apply):*  Death  Life-threatening  Resulted in or prolonged hospitalization  Required medical / surgical intervention to prevent serious outcome  Resulted in significant / persistent disability or incapacity Other:____________________ | **Date of event onset:**  \|____\|____\|/\|____\|____\|/\|____\|____\|  *day month year* | | | | **Maximum event severity:**  Mild  Moderate  Severe  Life-threatening |
|  | **Date of site awareness:**  \|____\|____\|/\|____\|____\|/\|____\|____\|  *day month year* | | | |  |
| **EVENT SUMMARY** *(include details of event, associated signs and symptoms, possible alternative etiologies, relevant past medical history, and medical management):*  *____________________________________________________________________________________________________________*  *____________________________________________________________________________________________________________*  *____________________________________________________________________________________________________________*  *____________________________________________________________________________________________________________*  *____________________________________________________________________________________________________________*  *____________________________________________________________________________________________________________* | | | | | |
| **Study product name:** Artemether-lumefantrine | | | **Route of study product:** Oral | | |
| **Dosing schedule at SAE onset:** | | | | | |
| **Date study product first started** *(Day 0)***:**  \|___\|___\|/\|___\|___\|/\|___\|___\|  *day month year* | | | **Date study product last taken prior to onset of SAE:**  \|___\|___\|/\|___\|___\|/\|___\|___\|  *day month year* | | |
| **Relationship to study product:**  None  Unlikely  Possible  Probable  Definite | | | **If not associated, is event related to:**  Study procedure  Other condition or illness  Other medication  Other____________________________ | | |

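### The serious adverse event form is built for artemether-lumefantrine alone, so causality for spraying and nets is graded only on the companion form H1, as one rating that cannot be split by intervention

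*Protocol*

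**What the plan says.** Appendix F is the side-effect form for insecticides. It asks the head of the house whether anyone there has had any listed symptom since the house was sprayed or nets were issued. For each person affected, staff are to "call up each participant and complete the adverse reporting form", and then: "If serious also complete the serious adverse event form".

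Form H1 in Appendix H is the adverse event form. Its header reads "CIRCLE AS APPROPRIATE:FSAT/ IRS/LLIN". Below it are five event rows with one relationship column, scored "Rank on scale of 0-4: none = 0; unlikely = 1; possible = 2; probable = 3; definite = 4", and a yes/no column for seriousness.

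The initial serious adverse event (SAE) report in Appendix H names the study product as "Artemether-lumefantrine" and the route as oral, both pre-printed. It asks for the dosing schedule, the date the product was first started, and "Date study product last taken prior to onset of SAE". It then asks for one graded relationship to the study product, from none to definite. A further item, to be used if the event is not associated, lists study procedure, other condition or illness, other medication, and Other with a blank. There is also a free-text event summary.

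On exposure, section 9d (Intervention) states that "IRS will be carried out twice per year in all households in the intervention hotspots" and that nets are given for each sleeping space there. AL is given where a resident has a positive rapid test, and not to pregnant women or to infants under 6 months (sections 9d and 9f). Section 11 has nets and focal screening and treatment (FSAT) rolled out together, with spraying immediately afterwards. Section 12c undertakes to monitor and document reported side effects of every intervention.

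**The concern.** A form designed for a drug taken by mouth has been reused for insecticide exposures without being adapted. Serious events after spraying or net distribution arrive at a page whose product, route, dates and graded relationship all refer to AL.

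This matters most where exposures overlap. A person in an intervention hotspot may receive AL and a net in the same period and have the house sprayed soon after. Follow-up for side effects then falls about a week after spraying and about a week after AL starts (section 9f). If that person has a serious event, the form gives one product a structured causality judgement and leaves the others to a tick or a narrative. A later tabulation of serious events by suspected intervention would rest on fields that exist for AL and not for IRS or LLIN. Insecticide reactions are not hypothetical in this plan: section 9f reports occasional itching with the insecticide used in the 2011 government programme.

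**Working it through.** No arithmetic beyond a count applies; the check sets the forms beside the exposures.

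**Step 1: what each form holds for each intervention on H1's header.**

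| Item | AL (FSAT) | IRS | LLIN |
|---|---|---|---|
| H1: intervention named | yes, circled | yes, circled | yes, circled |
| H1: relationship grade | one 0-4 rating per event row, tied to no named product | same rating | same rating |
| SAE initial report: product field | pre-printed | none | none |
| SAE initial report: exposure date | first start and last intake | none | none |
| SAE initial report: graded relationship | yes | none | none |
| SAE initial report: other structured route | not needed | study procedure or Other, if not associated | same |

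Of three interventions, one has structured product, date and graded-relationship fields on the SAE form: 3 − 1 = 2 do not.

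**Step 2: three cases through the forms.**

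1. *Spraying or a net, no AL.* This happens by design. IRS covers all hotspot households, while AL depends on a positive rapid test and excludes pregnant women and infants under 6 months. Appendix F asks about anyone in the house, so these people are covered. On the SAE form the product, route, schedule and date fields do not apply, and the relationship to study product is none. The tick list then opens, and study procedure or Other can be marked. The degree of relationship to the insecticide is graded only on H1.
2. *AL plus spraying or a net, AL judged unrelated.* The result is the same, with the AL dates filled in. The SAE form does not say whether a rating of unlikely counts as not associated.
3. *AL plus spraying or a net, AL judged possible, probable or definite.* The tick list no longer applies, because it is conditional on no association. A suspected contribution from spraying or the net has only the narrative on the SAE form. On H1 the event row has one rating. If FSAT and IRS are both circled, that number cannot be assigned to either.

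**Step 3: can case 3 occur?** Section 11 puts nets and FSAT in the same round, with spraying immediately after. Section 9f revisits houses about one week after spraying and follows treated people on treatment days and one week after AL starts. The exposure and reporting windows therefore overlap in the planned schedule. The protocol gives no figure from which to count such people.

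**Step 4: does the rest of the set help?** The SAE management report (H3) asks whether the study product's dose was unchanged, held or discontinued. That again presumes a dosed drug and adds no insecticide field. Appendix D records the date of net distribution by house and net, so that exposure date exists elsewhere, but not on the safety forms.

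**The case against.** The best defence is that the SAE form never stands alone. Appendix F says it is completed *also*, so H1 accompanies every serious insecticide event. H1 names IRS or LLIN, grades the relationship 0-4 without tying it to AL, flags seriousness, and instructs: "If serious, report to core facility staff immediately". The SAE form offers study procedure and Other, and its narrative asks for alternative causes. All of this stands, and it rules out several stronger readings:

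- A reader might infer that a serious reaction to spraying or nets cannot be attributed to them, or that the record can attribute events only to AL. The documents do not support this: H1, the tick boxes and the narrative each allow another cause to be recorded.
- A reader might infer that most exposed people have insecticide exposure only. The protocol gives no proportion of compounds or houses with a positive rapid test, so only *some* can be said.
- A reader might infer that insecticide events will be undercounted and AL events overcounted. No such bias is shown. A person who took no AL is rated none for AL, which is correct.
- All six named symptoms in Appendix F also appear in Appendix G. That is not a defect in itself. They are non-specific symptoms that both checklists need to ask about, and person identifier and onset date on H1 allow double entries to be matched.

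It can also be said that several ratings by field staff would not settle causality among near-simultaneous exposures. That is true, but separate ratings would at least record what was suspected. The defence does not answer case 3: once AL is rated possibly related, the SAE form has no structured place for a second suspect, and H1's single rating does not supply one.

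**Conclusion.** The mismatch is real and minor. Serious events after spraying or net distribution go to a form whose product, route, dates and only graded relationship belong to AL. Causality for IRS or LLIN is graded only on H1, as one unsplit rating. On the SAE form it is reduced to a tick or free text, and to free text alone where AL is rated as possibly related. Two of the three interventions on H1's header are affected.

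The conclusion rests on reading the forms as printed, on taking the tick list's condition literally, and on the section 11 timetable being followed. It concerns stated form content, not detail left to another document. It bears on how well the forms deliver the commitment in section 12c. Neither the primary nor the secondary outcome is a safety outcome, so the sample size and primary analysis are untouched.

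**What to change.** On the SAE initial report, replace the pre-printed product and route with one line for each intervention received: AL; IRS, with the insecticide named (section 9f leaves three candidates open); and LLIN. Give each line its own exposure date and its own relationship rating, so that a second suspected cause can be graded whatever rating AL receives. On H1, record the relationship separately for each intervention circled.

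The cost is a small redesign of two paper forms and slightly longer completion for each event. No extra visits, staff or samples are needed.

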**Appendix G: Adverse reporting monitoring form for FSAT**

Call up each participant treated, **one by one**.

Area (Cell)_____________

Compound/house code_______________

Participant’s ID,.

Partcipant Name______________

Year of birth_________________

Sex _________M/F

Ask the participant about how they took AL:

- - 1. What time did you take your Coartem last night?

*S: Je ulimeza (dawa ya malaria) coartem saa ngapi jana usiku?*

*L: Ni mwonyo coartem (yadh malaria) saa adi otieno manyoro?*

________________

- - 1. How did you take the drugs?

*S: Ulimezaje hizi madawa?*

*L: Nimwonyo yadhgi nade?*

________________

- - 1. Did you take the drugs with any food/fluids?

*S: Je ulimeaza madawa na chakula au kinyuaji chochote?*

*L: Be nimwonyo yath gi chiemo kata math moramora?*

________________

Then ask the participant the following questions e.g. “In the last 24 hours have you had a Headache?” Write down the answer in the relevant column, like this: put a (**Y**) for “Yes”, a (**N**) for “No” and a “**DK**“ for “Don’t know”. Continue with the next problem and record the answers until all have been asked about. For an adverse event (i.e. where Y is recorded)., document each event on the following adverse reporting form. If any event is termed as severe/life threatening complete the second serious adverse event reporting form as well.

Below are the questions translated into Luo, and Kiswahili.

| **Questions** | | | **(Y/N/DK)** |
| --- | --- | --- | --- |
| **ENGLISH** (In the last 24hrs have you had…….. | **LUO** (Kuom seche piero ariyo gi ang’wen mokalo, be isebdo gi….. | **KISWAHILI** (Kwa masaa ishirini na manne yaliyopita,je umehisi…… |  |
| **1.Headache** | Wich bar | Kuumwa na kichwa |  |
| **2. Itching/or rash** | Guonyruok/guonyo | Kuwashwa ama harara |  |
| **3. Difficulty in breathing** | Pek mar yueyo | Ugumu wa kupumua |  |
| **4.Fatigue/body weakness** | Jony mar del | Uchovu ama unyonge wa mwili |  |
| **5.Dizziness** | Kawirawira | Kusinziasinzia |  |
| **6. Muscular pain** | Rem mar leche | Maumivu ya misuli |  |
| **7. Joint pains** | Rem mar fuonde | Maumivu ya viungo |  |
| **8. Vomiting/nausea** | Ng’ok/chuny lep | Kutapika ama kuchafukwa na moyo |  |
| **9. Fever** | Liet mar del | Joto jingi |  |
| **10. Stomachache** | Ich kach | Kuumwa na tumbo |  |
| **11.Others/specify** | Mamoko/wachi | Mengineyo/fafanua |  |

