Treatment will be carried out using artemether-lumefantrine (Coartem, AL) according to national guidelines. AL is an antimalarial drug with an excellent safety profile; limited data on safety are available for children under 6 months and pregnant women, both groups will therefore be excluded from AL treatment (see below) but receive clinical care when necessary. As detailed below, all those who are given Coartem will be actively followed-up to monitor any side effects. This monitoring will happen on all days of treatment and one week after the start of treatment. If given to parasite-free individuals, AL will provide an effective prophylactic effect for 3-4 weeks, which has been shown to be highly beneficial for malaria control purposes in high endemic regions [36]. In parasite carriers, AL effectively clears asexual parasites and gametocytes, the parasite stage responsible for transmission [35]; the timing of FSAT is chosen to ensure individuals are parasite and gametocyte-free before the start of the peak transmission season. For those receiving AL, the first dose will be supervised and then instructions will be provided for taking of the second dose which will be issued. Teams will return to compounds the next day to administer and supervise the third dose and distribute the fourth. They will return again on the third treatment day to again administer and supervise the fifth dose and distribute the sixth. At the same time any side effects will be noted. (see appendix G & H).

All participants will be told their haemoglobin level immediately, and any person found to be anaemic will be provided haematinics according to national guidelines.

Treatment of risk groups: children <6 months and pregnant women

Children below 6 months of age will be excluded from the study; they will be screened for fever and referred to a health facility where needed but will not be included in FSAT.

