c. Risks to intervention participants

None of the interventions that are proposed in this study are experimental. LLINs and IRS are part of the malaria control efforts by the DOMC for the district; larviciding has been done in districts bordering or close to Rachuonyo district, in Nyando, Kisii, Suba and Kakamega districts [22]. All insecticides used will have been approved by DOMC and PCPB prior to application. The FSAT approach to screen asymptomatic children and treat all inhabitants of households where ≥1 individual is found parasite positive by RDT has not been done routinely in Kenya but is an extension of screening and treatment of asymptomatic individuals that is proposed under the Kenyan National Malaria Strategy for 2009-2017[[13](#_ENREF_13)]. The national strategy does not currently propose to treat household members of asymptomatic parasite carriers; the approach is justified by evidence of clustering of parasite carriage at household level [2, 6, 25, 33] and the low sensitivity of RDTs for detecting all epidemiologically relevant parasite densities [[14](#_ENREF_14)]. We will provide supervised treatment with the first line antimalarial drug AL that has an excellent safety profile and is recommended for treatment of symptomatic and asymptomatic malaria infections in Kenya [[13](#_ENREF_13)]. We will also closely monitor and document any reported side effects of all interventions by questionnaires on all days of treatment and one week after treatment, IRS and ITN distribution.

d. Benefits to survey participants

All participants of the cross-sectional survey will benefit from knowing their haemoglobin level and whether they have a clinical malaria infection. Any participant with low haemoglobin will receive treatment for anaemia. All individuals who are diagnosed with a clinical malaria episode will be treated with AL according to Kenya national guidelines.

e. Risks to survey participants

This survey is of minimal risk to participants. Blood will be collected by fingerprick only using a sterile lancet, and the total amount of blood collected is very small (200-300μl); participants may experience only a small bruise at the site where we collect the blood. Blood draws will be carried out by trained medical or laboratory staff members to ensure these are done in as safe a manner as possible.

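### The only FSAT side-effect checklist has a 24-hour stem; if it is used at the one-week contact, about four of the first seven days are not prompted

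*Protocol*

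**What the plan says.** **Schedule.** Protocol section 9f (Procedures: intervention phase), on side-effect follow-up of those given AL: "This monitoring will happen on all days of treatment and one week after the start of treatment". Section 12c (Risks to intervention participants) words it differently: "by questionnaires on all days of treatment and one week after treatment, IRS and ITN distribution".

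**Dosing visits.** The first dose is supervised and the second is left with the participant. Then: "Teams will return to compounds the next day to administer and supervise the third dose and distribute the fourth". On the third treatment day staff "again administer and supervise the fifth dose and distribute the sixth". The second, fourth and sixth doses are therefore taken unobserved.

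**FSAT form.** Section 9f refers to Appendices G and H for recording side effects. Appendix G gives the example "In the last 24 hours have you had a Headache", and its table of eleven items is headed "In the last 24hrs have you had", with the same period in Luo and Kiswahili. It opens with "What time did you take your Coartem last night". Only a Yes on this checklist leads to an entry on the adverse event form in Appendix H, which has a field for date of onset.

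**Insecticide form.** Appendix F asks about symptoms "since we sprayed the house/issued bednets", so its recall runs back to the intervention. Section 9f places the visit after spraying at about one week.

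**The concern.** A 24-hour question works when the team was there the day before. Asked once at one week, it reaches back one day only. A rash or a bout of vomiting that begins on day 3 and is over by day 5 would correctly be answered No, and no adverse event entry would follow.

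The dosing question has a similar limit. Asked on the day after an evening dose, it checks the second and fourth doses. No visit is planned between the sixth dose and the one-week contact, and by then the previous night is the wrong evening.

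What is at stake is the completeness of the safety data. AL is given to whole households, including people with no detectable parasites. Section 12c acknowledges that the national strategy does not currently propose treating household members of asymptomatic carriers, and it offers close monitoring by questionnaire alongside the drug's safety record.

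**Working it through.** The protocol states no coverage figure, so there is none to reproduce. The check lays the 24-hour recall windows over the visit schedule, in hours from the first dose.

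**Inputs**
- Treatment-day contacts at about 0, 24 and 48 h (section 9f: first day, next day, third treatment day).
- One-week contact at 168 h (section 9f, from the start of treatment), or at 48 + 168 = 216 h (section 12c, if counted from the last treatment day).
- Recall of 24 h at every contact (Appendix G). That Appendix G is the form used at one week is an inference: no other FSAT checklist is named.
- Assumption: the sixth dose is taken 8 to 12 h after the third treatment-day visit, that is at 56 to 60 h. The protocol gives no clock time.

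**Formula.** Uncovered time = total period − union of the recall windows after the first dose.

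**Contact at 168 h**
- Windows: 0–24, 24–48 and 144–168 h, which is 72 h covered.
- Uncovered: 168 − 72 = 96 h, running from 48 to 144 h. This is 4 of 7 days; 96/168 = 57%.
- Time from the sixth dose to the visit: 168 − 60 = 108 h to 168 − 56 = 112 h.
- Of that, 24 h are covered (24/112 = 21% to 24/108 = 22%), and 84 to 88 h (3.5 to 3.7 days) are not.

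**Contact at 216 h**
- Windows: 0–24, 24–48 and 192–216 h, again 72 h.
- Uncovered: 216 − 72 = 144 h, running from 48 to 192 h. This is 6 of 9 days.
- Time from the sixth dose to the visit: 156 to 160 h, of which 24 h (about 15%) are covered and 132 to 136 h (5.5 to 5.7 days) are not.

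**With recall since the last visit**
- Contact at 168 h: windows 0–24, 24–48 and 48–168 h cover all 168 h, so 0 of 7 days are uncovered.
- Contact at 216 h: the last window is 48–216 h, so again nothing is uncovered.

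**The case against.** **The protocol does not say that Appendix G is used at one week.** In section 9f the reference to Appendices G and H follows the description of the dosing visits, and the question about last night reads like a treatment-day question. This stands as a limit: use at one week is a strong inference, not stated text. The alternative is no better, because the protocol would then promise a one-week questionnaire and show none.

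**A reader might infer that nothing after the sixth dose is ever asked about.** The documents do not support that. The last 24 hours before the visit fall after the sixth dose and are asked about. An event that began earlier and is still present then would be marked Yes and entered in Appendix H with its onset date. Only events that both start and resolve in the gap go unprompted.

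**A reader might take 57% as the share of events missed.** It is a share of clock time. The protocol gives no distribution of event timing, so the size of any under-count cannot be derived.

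**Other routes of capture exist.** Participants can volunteer a complaint, a clinical officer is available to advise, there are separate serious adverse event forms, and the resolution date in Appendix H refers to Day 42. These soften the point, chiefly for serious events. None asks the participant systematically about the gap, and section 9f schedules no Day 42 visit.

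**The sixth dose is openly unsupervised, and its verification is not promised.** This is fair. The narrower point remains: the form asks a dosing question that, at one week, cannot answer whether that dose was taken. The other two dosing questions carry no time limit, but neither asks which doses were taken or when.

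**No trial estimate is affected.** Correct: adverse events are neither a primary nor a secondary outcome.

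**Conclusion.** The point holds in a limited form. If Appendix G is used unchanged at the one-week contact, events that start and resolve between about 48 and 144 h after the first dose are not prompted: about four of seven days. The gap is about six of nine days if section 12c is read as one week after the last treatment day. In both cases it covers all the time after the sixth dose except the 24 h before the visit, and completion of the course cannot be established from the dosing question.

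This rests on Appendix G being the one-week form, on treatment-day visits about 24 h apart, and, for the figures after the sixth dose only, on that dose being taken at 56 to 60 h. The consequence is incomplete capture of transient side effects, by an amount that cannot be quantified. The change is worth making because it is cheap and the protocol's own insecticide form already shows suitable wording.

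**What to change.** - State which form is used at the one-week FSAT contact, and provide a one-week version of Appendix G.
- On that version, replace the 24-hour stem with *since our last visit*, in all three languages. This follows the approach of Appendix F. The onset date field in Appendix H already allows events to be placed in time.
- On that version, replace the question about last night with one on whether and when the sixth dose was taken.
- Keep the 24-hour stem and the existing dosing question for the treatment-day visits.
- Reconcile sections 9f and 12c on whether the week is counted from the start of treatment or from its end.

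**Cost.** Rewording and re-translating one form, and slightly longer recall at one visit. No extra visits or staff are needed, and no treatment rule changes.
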